### Intervention Development and Framework

The development of the bTF-CBT-C intervention will follow the multiphase optimization strategy (MOST), a structured framework for developing and refining complex behavioral interventions [39,40]. MOST will be used to guide the preparation phase, including identifying core TF-CBT and compassion-focused components and contextual adaptations for adolescents in northern Sweden. The optimization phase will include iterative testing of web-based modules and therapist procedures, incorporating feedback from adolescents, caregivers, and clinicians to refine clarity, usability, and feasibility. The current pilot RCT will represent the evaluation phase, providing feasibility and acceptability data needed to finalize the intervention before a fully powered noninferiority trial.

### Cultural and Contextual Considerations

The intervention will be adapted to reflect cultural and contextual factors relevant to adolescents receiving mental health care in northern Sweden, including linguistic needs, local norms regarding help-seeking, and geographic considerations. Cultural tailoring will focus on ensuring accessibility, clarity, and relevance of both digital and therapist-led components. Therapist training will include a cultural competence module addressing minority and Indigenous perspectives, including Sámi cultural considerations. To support culturally responsive care, clinicians will incorporate brief questions inspired by the Cultural Formulation Interview to identify individual background factors that may influence engagement, communication, or treatment preferences. These adaptations are intended to strengthen relational safety and enhance feasibility and acceptability across diverse adolescent populations.

### User Involvement

User involvement will be integrated throughout the development and evaluation of the bTF-CBT-C intervention. Adolescents with lived experience of trauma, caregivers, and representatives from the Swedish user organization Hjärnkoll [41] will contribute to the design and refinement of the intervention and the trial procedures. Their input will inform the research plan, recruitment materials, application content, and the overall structure of the blended intervention program.

During the preparation phase, user representatives reviewed the preliminary research protocol, provided feedback on feasibility considerations specific to youth in northern Sweden, and participated in workshops to evaluate the clarity, accessibility, and acceptability of proposed modules. Their perspectives were incorporated into revisions of the intervention flow, digital components, and the caregiver involvement strategy.

User involvement will continue throughout the study, including consultation on implementation challenges, interpretation of qualitative findings, and dissemination of knowledge. This participatory approach aims to enhance ecological validity, cultural relevance, and acceptability across all phases of the project.

### Interventions

#### Overview

The two interventions share the same theoretical foundation in TF-CBT and its PRACTICE (psychoeducation, relaxation, affective modulation, cognitive coping, trauma narrative/exposure, in vivo mastery, conjoint caregiver-child sessions, and enhancing safety and future development) components [10,42] but differ in delivery format, structure, and focus on mechanisms.

Standard TF-CBT is delivered as therapist-led, clinic-based treatment, with sessions conducted in person at the clinic. bTF-CBT-C is delivered as a blended intervention that combines therapist-led sessions with planned digital components and the systematic integration of compassion-focused strategies.

#### Control Arm (Standard TF-CBT)

Participants randomized to the control arm will receive standard TF-CBT following the PRACTICE components [10,43]. Treatment will consist of approximately 12‐25 weekly therapist-led sessions delivered in person at the clinic. Only occasional individual sessions may be conducted via videoconferencing when required. Caregiver involvement will follow the procedures described in the TF-CBT manual.

Treatment fidelity in the control arm will be supported through adherence to the TF-CBT manual [10], regular supervision, structured session reports, and adherence checklists aligned with the PRACTICE components. These procedures mirror those used in the experimental arm to ensure comparable monitoring of treatment delivery.

#### Experimental Arm (bTF-CBT-C)

Participants randomized to the experimental arm will receive bTF-CBT-C. Treatment will consist of a blended intervention for adolescents and their caregivers that combines digital and therapist-led components, including therapist support during a web-based stabilization phase (via brief messaging and, if needed, stepwise escalation to telephone or videoconferencing) as well as approximately 7‐14 therapist-led sessions across the trauma processing and integration phases (primarily via videoconferencing with some in-person sessions). The intervention includes (1) a structured web-based stabilization phase, (2) systematic integration of digital modules throughout treatment, and (3) explicit incorporation of compassion-focused strategies targeting shame, self-criticism, and emotional safety. These mechanisms are expected to support engagement in trauma-focused work.

The intervention begins with an approximately 5-week stabilization phase delivered through structured web-based modules. Adolescents and caregivers have access to tailored application content relevant to their respective roles in treatment. This phase covers psychoeducation, relaxation, affective modulation, and cognitive coping and integrates compassion-focused strategies (eg, soothing rhythm breathing, compassionate imagery, and self-compassion exercises). Interactive exercises and nature-based mindfulness tasks aim to activate the soothing system and reduce threat-related responding. Gamified elements support engagement.

Following the stabilization phase, treatment continues with therapist-led trauma processing and integration components, including trauma narrative, cognitive restructuring, in vivo mastery, conjoint sessions, and safety planning, with caregiver involvement consistent with the TF-CBT model (C6-C9). Compassion-focused principles are applied throughout all phases of the intervention to support emotional safety and engagement.

While the intervention follows a predefined structure based on a manual, therapists can adapt pacing and delivery format (eg, videoconferencing or in-person sessions) based on clinical needs. Core treatment components are maintained and are considered mandatory for all participants. Deviations from the planned format (eg, missed sessions or reduced engagement) are systematically monitored and managed using a predefined, structured approach. To ensure consistency and transparency, adaptations are guided by predefined and clinically grounded principles, including symptom severity, participant engagement, and practical constraints such as geographic distance. Videoconferencing is used as the default format to enhance accessibility, particularly for participants in remote areas, whereas in-person sessions are prioritized when clinically indicated (eg, elevated risk, complex presentations, or reduced engagement). Missed or canceled sessions are systematically followed up, and the delivery format may be adjusted (eg, from videoconferencing to in-person sessions, or vice versa) to support continued engagement in treatment.

All adaptations to delivery format or pacing will be documented in structured treatment and session logs using predefined templates. Formal fidelity ratings are not included in this pilot study to minimize the burden on participants and therapists. Instead, fidelity will be supported through regular supervision, session reports, and adherence checklists aligned with the intervention manual. These checklists specify the delivery of core components within each treatment phase. Therapists will document the completion of core intervention components across phases, and adherence will be systematically reviewed in supervision to ensure that key elements are delivered as intended while allowing necessary adaptations.

A detailed description of modules, delivery format, and session content is provided in Table 2.

**Table 2. T2:** Overview of bTF-CBT-C^a^ delivery across phases and modalities.

Phase/module	Delivery mode	Delivery details	Purpose of the module
Stabilization			
(C0) Introduction	Web-based application and clinic session	Self-paced onboarding; one-to-two 60‐90-minute clinic sessions with youth and caregiver	Establish therapeutic alliance, clarify structure, and initiate safety planning
(C1) Trauma and compassion	Web-based application and videoconference	Self-paced module; one 45‐60-minute videoconference session with youth and caregiver	Promote shared understanding of trauma and compassion; reduce shame through psychoeducation
(C2) Well-being and compassion with the body	Web-based application	Self-paced module; optional messaging support	Activate the soothing system and increase bodily awareness for emotion regulation
(C3) Emotions and the compassionate mind	Web-based application	Self-paced module; optional messaging support	Strengthening emotional literacy and tolerance through compassionate framing
(C4) Compassionate thinking	Web-based application	Self-paced module for youth and caregiver/messages; optional messaging support	Support cognitive coping and reduce self-criticism via compassionate self-talk
(C5) Preparing for trauma narrative with compassion	Web-based application	Self-paced module; optional messaging support	Built emotional scaffolding and readiness for trauma work
Trauma processing			
(C6) Trauma narrative with compassionate	Videoconference or/and clinic session	Weekly 60‐90-minute sessions (15‐30-minute caregiver/45‐60-minute youth); 2‐5 sessions	Facilitate trauma processing with caregiver support and compassionate engagement
Integration and recovery			
(C7) In vivo mastery with compassion	Videoconference or/and clinic session	Weekly 60-minute sessions; 1‐4 sessions	Promote real-life exposure with compassion to reduce avoidance and increase agency
(C8) Conjoint child-parent session	Clinic session	One 60‐90-minute joint session	Strengthen relational safety, mutual compassion, and emotional connectedness
(C9) Future safety and compassionate imagination	Videoconference or/and clinic session	One 60‐90-minute final session	Support future orientation, relapse prevention, and valued direction through compassion

a bTF-CBT-C: blended trauma-focused cognitive behavioral therapy with compassion. bTF-CBT-C is a flexible intervention that can be adapted to individual needs.

### Therapists and Implementation

All treatment will be delivered by licensed clinicians (psychologists or licensed psychotherapists) who have completed formal training in TF-CBT. Before initiating the study, therapists will complete a protocol-specific training program covering the structure of the blended intervention, digital delivery procedures, and the integration of compassion-focused strategies.

To ensure high-quality implementation and treatment fidelity, therapists will receive regular supervision from senior TF-CBT and CFT clinicians throughout the trial. Therapists will also receive brief guidance on culturally responsive and context-sensitive practice to ensure that the intervention is delivered consistently and safely across participating sites.

### Outcome Measures

#### Overview

Outcomes are prioritized in line with recommendations for pilot and feasibility trials. The primary focus is on feasibility and acceptability, while clinical and process-related outcomes are exploratory and intended to inform estimates of variability and guide outcome selection for a future trial. All outcome assessments will follow the predefined SPIRIT schedule (Table 1), with weekly and mid-module measures described in Multimedia Appendix 1. To minimize participant burden, exploratory measures are collected at selected assessment time points.

As some instruments (eg, Trauma-Related Shame Inventory and Trauma-Related Guilt Inventory) have not yet been formally validated in Swedish samples, their performance will be explored within the pilot data. This will include examination of distributions, internal consistency (eg, Cronbach α), and patterns of missing data to assess feasibility and interpretability. Sensitivity analyses will also be conducted to explore the robustness of findings across measures, and results will be interpreted with appropriate caution.

#### Primary Outcomes

##### Feasibility

###### Overview

Feasibility will be evaluated by assessing the extent to which the intervention and study procedures can be delivered within routine child and adolescent psychiatric services. Indicators will include recruitment rate, retention at each major assessment point, adherence to therapist-led and digital components, data completeness, and the functioning of study logistics such as randomization and assessment procedures. Adverse events will be monitored throughout the study via youth, caregiver, and therapist reports.

###### Adverse Event Monitoring

Adverse events related to digital and therapeutic components will be monitored using brief weekly screening items completed by youth, caregivers, and therapists. Respondents will report occurrence and rate severity on a 0‐3 scale. Events will be documented and reviewed in accordance with safety procedures.

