Adverse events (youth, caregiver + therapist)			✓	✓	✓
Primary outcomes (acceptability)					
Satisfaction (youth + caregiver)				✓	
Therapeutic alliance (youth, caregiver, therapist)^d^			✓	✓	
Digital treatment evaluation (youth + caregiver)^d^			✓		
Exercise evaluation^d^			✓		
Qualitative interviews			✓	✓	✓
Exploratory and clinical outcomes					
PTSD^e^ symptoms (CATS-2^f^, CRIES-13^g^)	✓		✓	✓	✓
Dissociation (DSQ-12^h^)	✓			✓	✓
Self-compassion (CEASY-SE^i^)	✓		✓	✓	✓
Emotion regulation (DERS-16^j^)	✓			✓	✓
Depression/anxiety/suicidality (MADRS-Y^k^, RCADS^l^)	✓		✓	✓	✓
Progression criteria					
Recruitment ≥60%	✓				
Retention ≥70%			✓	✓	✓
Acceptability ≥4/5				✓	
Data completeness ≥80%			✓	✓	✓

a SPIRIT: Standard Protocol Items: Recommendations for Interventional Trials.

b bTF-CBT-C: blended trauma-focused cognitive behavioral therapy with compassion.

c TF-CBT: trauma-focused cognitive behavioral therapy.

d Repeated mechanism/process measures (eg, therapeutic alliance, digital treatment evaluation, exercise evaluation, shame visual analogue scale, Trauma-Related Shame Inventory/Trauma-Related Guilt Inventory) are collected throughout the stabilization and trauma phases. A detailed full schedule table with all weekly/mid-module assessments (T0-T9) is provided in Multimedia Appendix 1.

e PTSD: posttraumatic stress disorder.

f CATS-2: Child and Adolescent Trauma Screen, version 2.

g CRIES-13: Children’s Revised Impact of Event Scale, 13-item version.

h DSQ-12: Dissociative Symptoms Questionnaire, 12-item version.

i CEASY-SE: Compassionate Engagement and Action Scale for Youth – Swedish Version.

j DERS-16: Difficulties in Emotion Regulation Scale, 16-item version.

k MADRS-Y: Montgomery-Åsberg Depression Rating Scale for Youth.

l RCADS: Revised Child Anxiety and Depression Scale.

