### Safety Procedures

A structured safety plan will be collaboratively developed with each adolescent and caregiver during the first therapist-led meeting, prior to the web-based stabilization phase. The plan will outline individualized strategies for managing distress, suicidal ideation, self-harm urges, and other safety concerns. It will include coping strategies, caregiver involvement, and clear instructions for contacting clinical staff during working hours or emergency services if risk escalates outside these hours.

During the web-based phase, suicide risk and distress will be monitored weekly via digital self-report measures completed by adolescents and caregivers. Reports indicating increased risk (eg, escalating distress, suicidal ideation, or self-harm urges) will trigger an alert to the clinical team. A clinician will review the alert within 1 working day, contact the adolescent and caregiver to assess risk, and initiate appropriate actions.

Therapists will follow a predefined protocol for managing interrupted or terminated video sessions. In the event of an unexpected disconnection, the therapist will first attempt to reconnect immediately, then contact the adolescent by telephone. If contact cannot be established, standard welfare-check procedures will be initiated, including contacting caregivers and, if necessary, coordinating with local services or emergency interventions.

Adverse events will be monitored through structured reports completed by adolescents, caregivers, and therapists, documenting occurrence and severity. All safety-related events, including suicide-related concerns, will be documented in a study safety log and reviewed in supervision. Serious adverse events (eg, suicide attempts, psychiatric hospitalizations, or significant clinical deterioration) will be reported to the principal investigator.

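### The weekly adverse-event screen is limited to treatment-related events, a limit found nowhere else in the protocol and wider in scope for the blended arm

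*Protocol article*

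**What the plan says.** The Abstract and Table 1 place adverse events among the primary feasibility outcomes. Four places describe how they are captured.

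- **Adverse Event Monitoring** (under Primary Outcomes): "Adverse events related to digital and therapeutic components will be monitored using brief weekly screening items completed by youth, caregivers, and therapists". On what is entered, it says "Respondents will report occurrence and rate severity", on a 0-3 scale. It describes no relatedness rating, and it refers recorded events on to the safety procedures.
- **Feasibility, Overview**: "Adverse events will be monitored throughout the study via youth, caregiver, and therapist reports".
- **Safety Procedures**: "Adverse events will be monitored through structured reports completed by adolescents, caregivers, and therapists, documenting occurrence and severity", and then "All safety-related events, including suicide-related concerns, will be documented in a study safety log and reviewed in supervision".
- **Table 1**: one adverse-event row, ticked at T1, T2 and T3, naming the same three respondent groups and not split by arm.

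On delivery, the Interventions overview says of the control arm: "Standard TF-CBT is delivered as therapist-led, clinic-based treatment, with sessions conducted in person at the clinic". The Control Arm section adds: "Only occasional individual sessions may be conducted via videoconferencing when required". Planned digital components are described for bTF-CBT-C only.

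**The concern.** Only the Adverse Event Monitoring section describes the weekly instrument, and only that section ties adverse events to a cause. If it is followed as written, the weekly screen yields a count of treatment-related events, while the structured reports and safety log described elsewhere cover events whatever their cause. The article does not say which source supplies the primary outcome.

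The limit also does not weigh equally on the two arms. Both arms have a therapeutic component. Only bTF-CBT-C has planned digital components, so the same sentence takes in more there than in an arm treated in person with occasional video. Participants and therapists know the allocation, so any view on what caused an event is formed with that knowledge.

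At stake is the reading of the safety data. In a randomised comparison, the contrast between arms shows whether a treatment adds harm better than case-by-case attribution does, but only if events are counted alike in both arms. The pilot is meant to inform a noninferiority trial of a partly remote treatment for adolescents with PTSD. None of its four progression criteria concerns adverse events, so the descriptive summary is the main quantitative safety evidence carried forward.

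**Working it through.** **Scope, place by place.** The protocol states no adverse-event rate or threshold, so there is no figure to reproduce. The check is a comparison of text.

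| Place | Scope stated | Limited by cause? |
|---|---|---|
| Adverse Event Monitoring | weekly items on events tied to digital or therapeutic components | yes |
| Feasibility, Overview | adverse events over the whole study | no |
| Safety Procedures | structured adverse-event reports; log of every safety-related event | no |
| Table 1 | one row at T1, T2, T3 | no |

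One of the four limits scope by cause and three do not. None states a separate definition for each arm.

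**Two readings of the weekly items.** The items belong to Multimedia Appendix 1, which is not shown.

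1. The items ask about treatment-related events. Someone must then decide relatedness at or before entry, because no later attribution step is described, and the weekly count is narrower than the log.
2. The items are cause-neutral. The section then misdescribes the instrument, and related events cannot be separated afterwards because only occurrence and severity are recorded.

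Under either reading the section needs rewording.

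**Scope by arm.** In bTF-CBT-C the definition covers therapeutic and digital components. In the control arm it covers therapeutic components and, at most, an occasional video session. Two further points suggest that ascertainment could be unequal. The Digital Components section describes the application that delivers weekly self-report measures as part of bTF-CBT-C. Safety Procedures describes weekly monitoring of risk and distress for the web-based phase, which only that arm has. The article does not say how the control arm receives weekly items.

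**Illustration on assumed inputs.** With 20 per arm (Sample Size section), one participant is 1/20 = 5 percentage points. Assume that 6 of 20 in each arm truly have an event, and that a fraction f of those 6 falls outside the screen's scope. The expected number recorded is 6 × (1 − f).

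| f | Recorded | Proportion of 20 |
|---|---|---|
| 0 (cause-neutral items) | 6.0 | 30% |
| 0.25 | 6 × 0.75 = 4.5 | 22.5% |
| 0.50 | 6 × 0.50 = 3.0 | 15% |

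If f is 0.25 in one arm and 0.50 in the other, equal true rates appear as 22.5% against 15%, a difference of 7.5 points or 1.5 participants. Swapping the fractions reverses the sign. The wider definition alone would tend to raise the bTF-CBT-C count, but attribution habits could work the other way, so no direction is claimed.

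The standard error of such a difference is √(0.225 × 0.775/20 + 0.15 × 0.85/20) = √0.0151, about 12 points. The illustrated bias is therefore smaller than chance variation at this sample size.

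**The case against.** The strongest reply is that the protocol does not describe a causality filter. Respondents are asked for occurrence and severity only, and the phrase about components may name the topics the items cover. The actual items sit in an appendix, which is where a condensed article would leave them. This stands as far as it goes: the behaviour of respondents is not established. It does not remove the conflict in stated scope, which lies in the article itself.

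Second, Safety Procedures provides unrestricted structured reports and a log, and directs serious events to the principal investigator without a causality condition. This also stands. An event outside the weekly screen, such as self-harm that a family thinks has nothing to do with treatment, can still be logged once the team learns of it. What remains is that two sources of different scope serve one primary outcome, and that an event missed by the screen reaches the log only by another route.

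Third, there is one nominal definition and one table row, both arms have therapeutic components, and harms specific to the application can arise only where it is used. All true. The definition is nevertheless wider in one arm, and a count by arm would inherit that.

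Fourth, no between-arm adverse-event contrast is specified, the summary is descriptive, and no progression threshold depends on it. This limits the consequence. It does not make the counts comparable for readers, or for the planners of the later trial.

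**Conclusion.** The point holds as a conflict in the scope of a primary outcome. The weekly screen is described as limited by cause, while the other descriptions of adverse-event capture are not. The one stated definition reaches further in bTF-CBT-C, so weekly counts by arm may reflect ascertainment rather than harm.

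A reader might go further and infer three things that the document does not support:

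- **Respondents screen out events they consider unrelated.** No attribution step is described and the items are not shown, so this is a risk only.
- **The arms have different definitions.** There is one definition, with unequal reach.
- **Events are permanently lost.** The unrestricted reports and safety log may still capture them.

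The size is unknown. The illustrated range runs from no effect to a difference of 7.5 percentage points in either direction. It rests wholly on the assumed 30% true event proportion and the assumed 25% to 50% outside scope. It shows that bias is possible, not that this plan will produce it. The correction is worth making because it is cheap and concerns a primary outcome; it does not call the trial's design into question.

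**What to change.** Reword the Adverse Event Monitoring section to agree with Safety Procedures and the feasibility overview:

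1. The weekly items ask both arms, in identical words, about any adverse event since the last report, whatever its presumed cause.
2. Suspected relatedness (digital, therapeutic, other) is recorded in a separate field after the event has been entered.
3. The descriptive adverse-event summary by arm is based on all events. Related events and digital-specific events appear as secondary tabulations, the latter within bTF-CBT-C.
4. The safety log uses the same definition.

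If the items in Multimedia Appendix 1 are already cause-neutral and the same in both arms, the change reduces to correcting the description and adding the relatedness field.

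The cost is a few reworded items and one extra field, with more minor or unrelated events recorded. The Trial Status section reports 6 participants enrolled at submission in May 2026. The report should note that they may have started under the existing items. At that point 40 − 6 = 34 of the planned 40 (85%) were still to be enrolled.
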